### Main Outcome Measures

#### Kinematic Analysis

The maximum flexion and extension ROM, the timing of their occurrence, and angular velocities of the lumbar spine and right and left hips will be computed in asymptomatic and CNLBP participants during flexion and extension phases [12] of STS and its reverse. The ratios of the total movements of the lumbar spine to those of the right hip and to the left hip will be determined during STS movement and its reverse. These ratios indicate the relative contributions of the joint pairs throughout the ROM. These kinematic parameters will be assessed again in both intervention groups after intervention. Each STS and its reverse will be screened to determine visually the beginning and the end of the movement. A single investigator will follow the same rule for every participant; start of T12 anterior displacement and stop of S2 displacement. Sagittal lumbar and hip angles will be calculated following filtering of the raw data using a robust low-pass Butterworth filter (6 Hz) [45].

#### Relative Phase Angle Analysis

Relative phase angle (RPA) is considered a technique to quantify coordination patterns and variability in the dynamical systems theory approach [46]. The RPA can represent both temporal and spatial information continuously throughout the STS movement and its reverse [46]. The RPA will be used to measure interjoint coordination between the lumbar spine and dominant hip. Phase angle is defined as the inverse tangent of angular velocity/angular displacement and will be calculated for each data point through the entire cycle (phase angle *φ* tan^–1^ [angular velocity/angular displacement]). The RPA between 2 body segments, which represents the joint coordination, will be calculated continuously from the differences between the phase angles of 2 joints (dominant hip–lumbar spine) [12,46]. The dominant leg will be determined by asking the participants with which leg they prefer to kick a ball [47]. If the RPA is negative, the hip is lagging the lumbar spine, and if the phase difference is positive, the hip movement is leading the lumbar spine [12]. Maximum and minimum relative phase differences and their timing will be computed before and after intervention in CNLBP participants. Furthermore, the relative phase relationship between the lumbar spine and hips (relative phase difference; x-axis) versus each percent of movement (y-axis) for STS and its reverse will be displayed in plots before and after intervention.

### Statistical Analysis

Statistical analyses will be performed on a personal laptop using SPSS for Windows release version 21.0 (IBM Corp) and STATA version 13 (StataCorp LLC). The comparability of asymptomatic participants and CNLBP patients on disability level, pain intensity, and kinematic variables at baseline will be analyzed using the independent *t* tests for parametric and Wilcoxon test for nonparametric distribution. In addition, a mixed-model 2-way analysis of variance (ANOVA) for each dependent variable (disability level, pain intensity, maximum joints ROM, joint angular velocities, lumbar/hip motion ratios, and maximum and minimum relative phase differences), with the 2 factors being group (core stabilization/general exercise) and time (preintervention/postintervention). After intervention, comparison between core stabilization group, general exercise group, and asymptomatic participants will be made using the ANOVA test (*Scheffe* post hoc tests). In addition, an intention-to-treat analysis will be conducted if any protocol deviation is observed at the end of the study due to attrition or loss to follow-up. Perceived pain and functional disability will be compared with consensus standards for minimal clinically important change (MCIC) [48]. Ostelo et al [48] considered the MCIC for VAS as 15 mm and for RMDQ as 5 points for patients with LBP. Furthermore, effects sizes will be measured using the Cohen *d* [49]. Statistical significance level is set at *P* ≤.05.

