**Results:**

Funding for the study was provided in 2016 by Iran University of Medical Sciences. The study is expected to last approximately 12 months, depending on recruitment. Findings on the study’s primary outcomes are expected to be finalized by December 2017. The results of the study will be published in a peer-reviewed journal.

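### No primary outcome is named among 22 to 34 dependent variables, each tested at P ≤.05, so the 5% error rate does not cover a claim of an exercise effect

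*Protocol article*

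**What the plan says.** The Statistical Analysis section plans "a mixed-model 2-way analysis of variance (ANOVA) for each dependent variable", with group (core stabilization or general exercise) and time (before or after intervention) as factors. The variables are listed as "disability level, pain intensity, maximum joints ROM, joint angular velocities, lumbar/hip motion ratios, and maximum and minimum relative phase differences". One threshold closes the section: "Statistical significance level is set at *P* ≤.05". The section does not rank the variables or adjust across them. Scheffe post hoc tests are planned for the post-intervention comparison of the two exercise groups and the asymptomatic group.

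Under Main Outcome Measures, the Kinematic Analysis subsection names "The maximum flexion and extension ROM, the timing of their occurrence, and angular velocities of the lumbar spine and right and left hips", computed "during flexion and extension phases [12] of STS and its reverse", and the ratios of lumbar motion to right and to left hip motion. The Relative Phase Angle Analysis subsection adds the maximum and minimum relative phase difference between lumbar spine and dominant hip. The Results paragraph of the Abstract says that findings on the "primary outcomes are expected to be finalized by December 2017", in the plural, and no section says which outcomes these are. The sample size under Participants is taken from another study and is not tied to any listed variable.

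**The concern.** The Discussion states the main question as whether core stabilization improves kinematic variables during sit-to-stand and its reverse. With no variable singled out, the article leaves open which result would answer that question. When many variables are each tested at 5%, some significant results are expected by chance, and nothing in the plan separates these from the result the trial was set up to deliver. The article expects more than description: it states directional hypotheses, classes itself as level Ib evidence, and hopes that a more favourable exercise programme could guide treatment. A chance finding among 15 patients per arm could therefore become the headline conclusion, with an error rate well above the 5% the reader would assume.

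**Working it through.** **Inputs from the article**
- Threshold: 0.05 for every test (Statistical Analysis). Sidedness is not stated; two-sided is assumed.
- Joints: 3 (lumbar spine, right hip, left hip). Movements: 2 (sit-to-stand and its reverse). Phases: 2 (flexion, extension).
- Arms: 15 patients each, 1:1 (Participants).

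**Input that is assumed**
- Correlation between variables. The article gives none, so a common value of 0, 0.3, 0.5 and 0.7 is shown.

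The article states no number of tests and no family-wise error rate, so there is no figure of its own to reproduce.

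**Count of variables in the ANOVA list**

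| Family | Without phase split | With phase split |
|---|---|---|
| Maximum ROM | 3 × 2 = 6 | 3 × 2 × 2 = 12 |
| Angular velocity | 3 × 2 = 6 | 3 × 2 × 2 = 12 |
| Lumbar/hip ratios | 2 hips × 2 = 4 | 4 |
| Relative phase (max, min) | 2 × 2 = 4 | 4 |
| Pain, disability | 2 | 2 |
| Total k | **22** | **34** |

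The split follows from the Kinematic Analysis subsection. The list in Statistical Analysis does not repeat it, so both counts are kept.

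**Expected false-positive interactions with no true difference between exercise groups:** k × 0.05 = 1.1 (k = 22) or 1.7 (k = 34).

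**Chance of at least one, either direction.** If independent, 1 − 0.95^k: 1 − 0.95^22 = 67.6% and 1 − 0.95^34 = 82.5%. For a common correlation ρ the test statistics share one normal factor u, and the chance is 1 − ∫ φ(u) [Φ((1.96 − √ρ u)/√(1−ρ)) − Φ((−1.96 − √ρ u)/√(1−ρ))]^k du.

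**Chance of at least one that favours core stabilization.** This uses only the upper 0.025 tail, with every variable coded so that benefit is positive. If independent it is 1 − 0.975^k; otherwise the same integral is taken with the upper limit only.

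| ρ | Either direction, k = 22 | k = 34 | Favouring core, k = 22 | k = 34 |
|---|---|---|---|---|
| 0 | 67.6% | 82.5% | 42.7% | 57.7% |
| 0.3 | 56.9% | 69.9% | 29.6% | 37.3% |
| 0.5 | 43.9% | 53.5% | 22.1% | 26.9% |
| 0.7 | 30.1% | 35.4% | 15.0% | 17.7% |

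The either-direction chance falls below one half at ρ of about 0.41 for 22 variables and 0.54 for 34.

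**Checks for k = 34.** Simulated t tests with 15 per arm (20,000 runs) give 54.5% at ρ = 0.5 and 36.6% at 0.7, close to the integral. Correlation of 0.7 within families and 0.2 to 0.3 between them gives 56% to 58%. If a time effect also counts as an exercise effect, with no true effect of either kind, the chance of at least one result of either type is 78% at ρ = 0.5 and 59% at 0.7.

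**The case against.** **The size depends on an assumption.** This stands. Right and left hips in a bilateral task, ROM and velocity of the same joint, and ratios built from the same motions may be strongly correlated. A reader might infer that a chance finding is more likely than not. The article does not support that as a general statement: it depends on the correlation and on the count, and it fails at ρ = 0.5 with 22 variables and at ρ = 0.7 with either count. For results favouring core stabilization alone, it fails at every correlated value shown.

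**The count could be pushed too high.** A reader might add the timing variables. They are to be computed, but they are absent from the ANOVA list, so no group-by-time test of them is stated. Nor does the article say which variables enter the post-intervention three-group ANOVA, so it cannot be assumed that every variable is tested again there.

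**No rule says that one significant variable is enough.** True; the article has no such success criterion. It has no other criterion either. Cohen d is planned, and pain and disability are to be compared with minimal important changes of 15 mm and 5 points, but these thresholds cover only two variables, neither of them kinematic.

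**Scheffe already adjusts.** Only among the three groups within one variable, not across variables.

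**This is a small thesis study described in a condensed article, and a full analysis plan may deal with multiplicity.** That weakens a complaint about missing adjustment taken alone. But the article itself lists the tests, fixes one threshold, groups all kinematic and phase variables as main outcomes, and refers to primary outcomes that it never identifies. The point rests on that text.

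**Conclusion.** The concern holds. Followed as written, the plan tests 22 to 34 variables at P ≤.05 with no named primary outcome. The chance of at least one false-positive group-by-time interaction is 30% to 83% over both counts and correlations from 0 to 0.7. For results favouring core stabilization alone it is 15% to 58%, against a nominal 2.5% for one test in that direction. Time effects read as an exercise benefit would raise these figures. They assume no true difference between the exercise groups on any variable, two-sided tests, and a common correlation that the article does not supply. The defect does not depend on passing 50%: the lowest either-direction figure is about six times the nominal 5% (30.1/5 = 6.0).

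**What to change.** Before data are seen, name one primary variable and one primary contrast, the group-by-time interaction for core stabilization versus general exercise, tested at 0.05. The sponsor should choose the variable. Apply Holm to a short, listed set of key secondary variables. Keep all other variables, including both hips, as exploratory, with estimates and 95% confidence intervals and no claim of significance. No measured outcome needs to be dropped: using only the dominant hip would be a preference, not part of the correction.

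This changes the text on outcomes and analysis, and leaves data collection and the number of patients as they are. The cost is that secondary variables need stronger evidence to be called significant. Adjusting over all variables would cost far more: Bonferroni over 34 tests gives 0.05/34 = 0.00147 per test and, with 15 per arm, raises the standardized difference detectable with 80% power from 1.06 to 1.62. That is why a single named primary variable and a short secondary list are preferable.

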### Participants

A total of 30 patients with CNLBP and 15 demographically matched asymptomatic (healthy) participants will be recruited for COSCIOUS. The sample size of CNLBP patients is determined based on previous studies that have evaluated the effect of lumbar extension exercise on the kinematics of the lumbar spine and hips during a common daily activity [25,26]. Steele et al [26] calculated the sample size for their study and reported that a minimum of 7 participants would be required in each group to achieve 80% power at an alpha level of *P* ≤.05 [26]. Therefore, 45 participants will be divided into 3 groups: 2 experimental groups (15 patients with CNLBP in each group) and one healthy control group (15 asymptomatic participants). Considering some attrition, the sample size was increased to 15 participants in each group. The CNLBP patients will be identified and recruited by posters, emails, and word of mouth from the university and the surrounding locality. Direct referral also will be provided from 2 orthopedic surgeons and 2 neurologists in Tehran. Inclusion criteria of COSCIOUS are as follows:

CNLBP (LBP persisting for more than 3 months in the absence of an underlying pathology)Aged between 18 and 40 yearsPain between 3 and 6 at rest on a 0- to 10-point pain visual analog scale (VAS), where 0 represents no pain and 10 is the worse pain imaginableAbility to perform STS movement and its reverse without an aidNo contraindication for exerciseNo obvious deformity of the spine, pelvis, and lower extremitiesNo autoimmune diseases (eg, rheumatoid arthritis) [12]No pregnancy

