In this study, we will try to balance some of most important prognostic indicators of LBP such as educational status, smoking, working status, age, gender, and pain intensity in 2 treatment groups [27,28]. This strategy will help minimize the effects of confounding variables. Participants who do not complete the treatment sessions (absence for 3 consecutive or a total of 5 sessions) will be excluded from the study. Before participation in this study, procedure of this investigation will be explained both verbally and in writing, and written informed consent will be obtained from all participants. In addition, the participants will be assured that their personal information will be kept confidential (confidentiality principle). Participants will be identified only by initials and participant number on the research notes. All study results and completed questionnaires will be anonymized. All trial documents will be stored securely and not accessible to people outside of the research team. Participants will be withdrawn from this investigation if there are any concerns regarding informed consent.

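### Neither planned comparison of the two randomised arms adjusts for baseline, which costs precision at 15 patients per arm unless pre-post correlation is very high

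*Protocol article*

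**What the plan says.** The Statistical Analysis section of the protocol article plans "a mixed-model 2-way analysis of variance (ANOVA) for each dependent variable" (disability, pain, joint ROM, angular velocities, lumbar/hip ratios, and maximum and minimum relative phase differences), "with the 2 factors being group (core stabilization/general exercise) and time (preintervention/postintervention". It does not say which term of that model tests the arm effect.

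The same section plans a second analysis containing both arms: after treatment, a "comparison between core stabilization group, general exercise group, and asymptomatic participants will be made using the ANOVA test", with Scheffé post hoc tests. No baseline covariate is described for either analysis, and ANCOVA is not mentioned in the article.

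The Participants section plans "2 experimental groups (15 patients with CNLBP in each group". The Procedure section places the kinematic assessment before random allocation, and Statistical Analysis treats pain and disability as baseline variables too. The Participants section also says that the team will try to balance several prognostic factors between the treatment groups, including pain intensity, and adds: "This strategy will help minimize the effects of confounding variables". That sentence concerns the make-up of the groups and does not bear on the analysis model.

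**The concern.** A change-score test subtracts the whole baseline value from each patient's result, so it fixes the slope of post on pre at 1. A post-only test fixes that slope at 0. When the true slope lies between, each leaves in noise that a fitted slope would remove. With 15 patients per arm, precision is scarce and chance baseline differences can be sizeable.

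The two planned comparisons also treat baseline in opposite ways. They can give different answers for the same outcome, and the article does not say which governs. At stake are the power and the clarity of the core-versus-general comparison, the only randomised contrast in the trial.

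**Working it through.** **The plan's own figure.** The Participants section cites another study for "a minimum of 7 participants would be required in each group to achieve 80% power at an alpha level of *P* ≤.05", then raises the number to 15 for attrition. It gives no effect size, SD or test, so the 7 cannot be reproduced. Solving backwards with a two-sided two-sample t test, 7 per group has 80% power for a difference of about 1.63 SD. At 15 per group the corresponding difference is 1.06 SD, which is the reference value below.

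**Inputs from the article.** 15 per arm (N = 30), 1:1 allocation, one pre and one post value per outcome, significance level .05.

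**Assumptions.** Two-sided testing, equal SDs before and after, all 30 patients analysed, and r from 0.3 to 0.9. The documents supply neither r nor SDs.

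**Step 1: what the interaction tests.** With two time points, the group-by-time F on 1 and 28 df equals the square of the two-sample t on change scores. In one simulated data set both came to 24.297.

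**Step 2: variances, relative to a post-only comparison with variance 1.**
- Change score: 2(1 − r)
- ANCOVA, large sample: 1 − r²
- Cost of estimating the slope: multiply by 1 + 1/(N − 4) = 27/26 = 1.038, and use 27 df
- ANCOVA/change ratio: (1 + r)/2 × 27/26. For example, at r = 0.5 this is 0.75 × 1.038 = 0.78.

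**Step 3: results.** Power is from the noncentral t, for an assumed true difference of 0.8 SD. Equivalent n is 15 divided by the variance ratio: the number per arm that a change-score test would need to match ANCOVA at 15.

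| r | Variance ratio, ANCOVA/change | Detectable at 80% power, change → ANCOVA (SD) | Power at 0.8 SD, change → ANCOVA | Equivalent n per arm |
|---|---|---|---|---|
| 0.3 | 0.68 | 1.25 → 1.03 | 43% → 58% | 22 |
| 0.5 | 0.78 | 1.06 → 0.94 | 56% → 67% | 19 |
| 0.7 | 0.88 | 0.82 → 0.77 | 78% → 83% | 17 |
| 0.8 | 0.94 | 0.67 → 0.65 | 92% → 93% | 16 |
| 0.9 | 0.99 | 0.47 → 0.47 | 99.7% → 99.7% | 15 |

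Simulation of 20,000 trials at each of r = 0.3, 0.5, 0.7 and 0.9 agreed: variance ratios 0.68, 0.79, 0.89 and 0.99.

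**Step 4: break-even.** (1 + r)/2 × 27/26 = 1 gives r = 52/27 − 1 = 0.93. Above that, ANCOVA is marginally less precise than the change score.

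**Step 5: the post-only comparison.** Against a plain two-arm post-only test, the ANCOVA variance is (1 − r²) × 27/26: 0.945 at r = 0.3, 0.78 at 0.5, 0.53 at 0.7 and 0.20 at 0.9. So where the change score loses little, the post-only contrast loses most.

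**Step 6: unequal SDs.** Let b = r × SD(post)/SD(pre) be the slope of post on pre. In large samples the change-score variance exceeds the ANCOVA variance by an amount proportional to SD(pre)² × (1 − b)². The gain therefore vanishes when b is near 1, whatever r is. For example, SD(pre)/SD(post) = 0.5 with r = 0.5 gives b = 1 and no gain.

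**The case against.** The strongest reply is that nothing here is an error. Under randomisation the change-score test is unbiased and keeps its type I error, as does the post-only test. That stands. A reader might infer that the planned analysis is invalid or biased by baseline imbalance; the documents do not support this, and the point is about precision only.

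The second reply is that the size is unknown. This also stands. The article averages three repetitions, has one investigator place all markers, and quotes a reliability of 0.86 for the disability questionnaire. That figure is not a pre-post correlation over a course of treatment, but if r were that high the variance would fall by only about 3.5% (0.93 × 1.038 = 0.966). Equal SDs are also doubtful for pain, because entry is restricted to 3 to 6 on a 0 to 10 scale. That may narrow the baseline spread relative to the post-treatment spread and push the slope towards 1. On the other side, markers are repositioned by palpation, foot placement is free and speed is self-selected, so a correlation above 0.9 across all the outcomes cannot be presumed.

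A reader might also infer that the group main effect will be read as the arm effect. Because it averages in the pre-treatment value, its simulated power at 0.8 SD is only 20% to 26%. The article does not say this will be done, and the interaction is the natural reading. What remains is that the deciding term is unnamed.

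**Conclusion.** The point holds as a loss of efficiency that should be repaired. The article commits to a specific model and factors, so this is a stated choice and not a detail left to an analysis plan.

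Under equal SDs, the loss against ANCOVA is substantial at r up to about 0.5, modest at 0.7 to 0.8, and essentially nil from about 0.9, or wherever the slope of post on pre is near 1. It would be too strong to promise a fixed percentage of extra patients at no cost: that needs a known r and the large-sample formula, and at 30 patients the slope has to be paid for. That ANCOVA is usually the more precise choice is well established; the size of the gain in this trial is an assumption.

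**What to change.** In Statistical Analysis, specify that for each outcome core stabilisation and general exercise are compared by ANCOVA, with the post-intervention value as response and arm and the baseline value of the same variable as predictors. Report the adjusted difference with its 95% CI. Name this as the test of the arm effect, replacing both the group-by-time interaction and the core-versus-general Scheffé contrast. The time term and the comparison with asymptomatic participants may stay as descriptive analyses.

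The cost is a sentence or two of text, one degree of freedom per model, and a marginal loss of precision for any outcome whose slope is very close to 1. No new data are needed. The change gives one arm estimate per outcome; it does not settle how many outcomes are tested.

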Macedo et al [24] mentioned that core stabilization exercise can optimize the control and coordination of the spine. However, there is not sufficient evidence to clearly support this claim that core stabilization exercise has superior effects on joint coordination compared to general exercise. Therefore, the secondary objective of this study is to determine the effect of general exercise on the kinematics and joint coordination during STS and its reverse in CNLBP. We hypothesized that there are significant differences between the results in patients with CNLBP and healthy participants during STS and stand-to-sit movements. In other word, ROM, maximum displacement, and angular velocity of the lumbar spine and hips would be decreased in CNLBP. Furthermore, we hypothesized that exercise therapy would have a significant positive impact on the kinematics and coordination in CNLBP patients. It is hoped that COSCIOUS would help clinicians and physical therapists evaluate the functional disabilities of patients with CNLBP, who are a big population in LBP patients. In addition, we hope that if this study exercise therapy protocol has a more positive effect on the kinematics and joint coordination, it can be used as a guideline for the treatment of functional disabilities (especially this important functional movement) in populations with CNLBP.

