## Methods

### Study Design and Ethics

COSCIOUS is a parallel, randomized, double-blind controlled trial with 2 experimental groups and one asymptomatic (control) group. It is a part of the PhD thesis of the first author ([name]) and will be conducted in the biomechanics laboratory located at the School of Rehabilitation Sciences, Iran University of Medical Sciences (Tehran, Iran). The level of evidence of this investigation is level Ib. Ethical review and approval for COSCIOUS was obtained from the Research Ethics Committee at Iran University of Medical Sciences (Ethical Approval Number: IR.IUMS.REC 1395.9211342207) on July 27, 2016. The trial is registered at the Iranian Registry of Clinical Trials [IRCT2016080812953N2].

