### Randomization

Each CNLBP participant will be randomized to a general exercise group or a core stabilization exercise group with a ratio of 1:1. Randomization will be performed using a block-balanced randomization technique with 4 character blocks containing letters A and B. After randomizing, the randomization schedule will be transferred into written instructions and will be placed in sequentially numbered, opaque, sealed envelopes. The CNLBP participant will be blinded to which intervention group they are in until the end of the study. The procedure will be performed by an investigator who will not be involved with participant assessment, allocation, or treatment. The randomization schedule is known only to a physical therapist who treats the patients. The male physical therapist ([name]) assessing participants before and after the treatment will also be blinded to group allocation, and the patients will be asked not to disclose this to the physical therapist.

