### Procedure

#### Initial Assessment

After the recruitment process is complete and agreement to participate is obtained, participants will be brought into the biomechanics laboratory of the School of Rehabilitation Sciences, Iran University of Medical Sciences (Tehran, Iran). To ensure the activity is as natural as possible, few constraints will be placed on the procedure of STS movement and its reverse. Participants will not be allowed to use their hands to push up, and the feet should stay on the floor [12]. In order to standardize head posture and prevent the negative impact of the thoracic and cervical spines on lumbar spine kinematics, a visual target (white A4 paper with a black circle drawn upon it) will be adjusted to eye level in front of participants [31]. Data collection will begin with the capture of a reference standing posture. Then, participants will be asked to sit in their usual posture on an adjustable stool with neither armrest nor backrest. The stool provides support from the ischial tuberosities to the middle of the thighs. Foot placement will not be restricted and participants will be requested to relax their arms, hanging them next to their thighs. The stool height is 110% of knee-floor length, which is defined as the distance between the floor and the apex of the fibular head [12]. Participants will be instructed to stand up at their self-selected normal speed following a loud voice command (“Start”) and remain a comfortable and erect posture for 3 seconds. They will then be asked to sit down on the chair at their own comfortable speed and maintain this position for 3 seconds. Each subject will repeat the movements 3 times, and the mean data will be used for statistical analysis. Asymptomatic participants will serve as a control group in the first assessment in order to detect differences in kinematic parameters during STS and its reverse between the CNLBP patients and asymptomatic participants. Hence, they will not participate in the intervention phase and the second assessment (Figure 1).

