## Discussion

### Overview

To the best of the authors’ knowledge, this is the first time an investigation will evaluate the effects of core stabilization exercise on the kinematics and joint coordination of the lumbar spine and hip during STS and its reverse in patients with CNLBP. STS movement and its reverse are important functions required for conducting activities of daily living. Previous study has shown that these skills would be impaired in acute LBP [12]. However, the effects of CNLBP on flexion and extension phases of STS and its reverse is not well known, and COSCIOUS aims to investigate this issue.

Physical therapy programs play a key role in multimodal treatment approaches for CNLBP [50]. Therapeutic exercise is one of the few clearly effective physical therapy treatments to relieve pain for adults with CNLBP [50,51]. The European guidelines for the management of CNLBP suggest supervised exercise therapy as a first-line treatment [52]. In this investigation, the effect of the 2 most common types of therapeutic exercises prescribed for patients with LBP will be evaluated on the kinematics and joint coordination of functionally important activities. To the best of authors’ knowledge, no published study has assessed the effect of exercise therapy on STS movement and its reverse. The main study question is whether core stabilization exercise programs are effective in improving kinematic variables during STS and its reverse in CNLBP. In addition, a comparison will be made between the results of the 2 therapeutic exercises on STS and its reverse. The results of COSCIOUS will provide some insight into the effects of CNLBP on lumbar spine–hip coordination of activities of daily living.

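### The main question asks whether core stabilisation works, but the only randomised contrast is core versus general exercise; the analyses that could speak to effectiveness itself are uncontrolled

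*Protocol article*

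**What the plan says.** The Discussion (Overview) states the aim: "The main study question is whether core stabilization exercise programs are effective in improving kinematic variables during STS and its reverse in CNLBP". The comparison of the two programmes follows as a further item: "In addition, a comparison will be made between the results of the 2 therapeutic exercises on STS and its reverse". The Introduction frames matters the same way. It says "we hypothesized that exercise therapy would have a significant positive impact on the kinematics and coordination in CNLBP patients", and it adds that "the secondary objective of this study is to determine the effect of general exercise on the kinematics and joint coordination". Each of these concerns a programme's own effect.

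Study Design and Ethics describes a "parallel, randomized, double-blind controlled trial with 2 experimental groups and one asymptomatic (control) group". Under Randomization, "Each CNLBP participant will be randomized to a general exercise group or a core stabilization exercise group with a ratio of 1:1". No group of patients goes without exercise. Initial Assessment says of the asymptomatic participants that "they will not participate in the intervention phase and the second assessment".

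Statistical Analysis plans two analyses that bear on treatment:

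- a mixed two-way ANOVA in the patients, with factors group (core, general) and time (pre, post);
- a three-group comparison with Scheffé post hoc tests: "After intervention, comparison between core stabilization group, general exercise group, and asymptomatic participants will be made using the ANOVA test".

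**The concern.** A trial that randomises between two active programmes can show that one is better than the other. It cannot show by randomisation that either one works. If both work equally well the interaction is null, and if neither works it is also null.

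That leaves two places in the plan from which effectiveness could be read. The time effect has no concurrent untreated patients, so natural course, attention and familiarity with the test all count towards it. The three-group ANOVA compares patients at their second assessment with people seen once, before any treatment, so health status is mixed up with treatment, elapsed time and repeat testing. A non-significant difference there invites the reading that patients have recovered. The same ANOVA also gives a second answer on core versus general, from post-treatment values alone, and the Statistical Analysis section does not say which answer governs.

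At stake is what the trial may conclude. The Introduction hopes that the programme could guide treatment, and a significant time effect could be offered in support of that.

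**Working it through.** **Inputs.** From the protocol article: 15 patients per exercise arm, 30 in all; one pre and one post assessment in patients; one baseline assessment in the asymptomatic group; significance at 0.05 (taken as two-sided). Assumed, because the document gives no figures: a non-exercise change m common to both arms of 0.2 or 0.3 SD; a pre-post correlation r of 0.5, 0.7 or 0.8; no dropout. The document has no figure of its own on this point to reproduce.

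**1. Time effect when exercise does nothing.** The SD of change is √(2(1−r)) in units of the outcome SD, so the standardised change is dz = m/√(2(1−r)). For m = 0.3:

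- r = 0.5: 0.3/√1.0 = 0.300
- r = 0.7: 0.3/√0.6 = 0.387
- r = 0.8: 0.3/√0.4 = 0.474

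Probability of a significant pre-post test, from the noncentral t distribution:

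| Drift m | Test | r = 0.5 | r = 0.7 | r = 0.8 |
|---|---|---|---|---|
| 0.2 SD | core arm, n = 15 | 0.11 | 0.15 | 0.21 |
| 0.2 SD | pooled time effect, n = 30 | 0.18 | 0.28 | 0.39 |
| 0.3 SD | core arm, n = 15 | 0.19 | 0.29 | 0.40 |
| 0.3 SD | pooled time effect, n = 30 | 0.36 | 0.54 | 0.71 |

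The core-arm rows match the main question about core stabilisation. The pooled rows match the Introduction's wider hypothesis about exercise therapy. A simulation of 20,000 trials (r = 0.5 and 0.7) agrees to within about one percentage point. With m = 0 both tests are significant about 5% of the time.

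**2. Interaction under the same conditions.** A drift common to both arms cancels in the difference between arms. In the simulation the interaction was significant in 4.7% to 5.2% of trials at every drift from 0 to 0.5 SD.

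**3. Three-group ANOVA when exercise does nothing.** Assume that patients have a true deficit of D SD that exercise leaves unchanged, with 15 per group. The Scheffé comparison of core with asymptomatic participants is non-significant in 86% of simulated trials at D = 0.5, 62% at D = 0.8 and 42% at D = 1.0. A result of no detectable difference from healthy people is therefore common without any recovery.

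**4. Precision of core versus general.** Relative to outcome variance σ², the between-arm comparison uses

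- change scores (the planned interaction): 2(1−r)σ²
- baseline-adjusted post values (ANCOVA): (1−r²)σ²
- post values alone (the three-group ANOVA): σ²

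Interaction over ANCOVA is 2(1−r)/(1−r²) = 2/(1+r): 2/1.5 = 1.33 at r = 0.5 and 2/1.7 = 1.18 at r = 0.7. Post-only over ANCOVA is 1/(1−r²): 1/0.75 = 1.33 and 1/0.51 = 1.96. The post-only test of randomised arms is unbiased but wasteful.

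**The case against.** The strongest reply is that a valid randomised test is already planned. The interaction holds its error rate under any shared drift, and Statistical Analysis nowhere says that the time effect answers the main question. The Introduction also gives a comparative motive: it notes the lack of good evidence that core stabilisation is superior to general exercise for joint coordination. Read that way, the interaction is the right test and the fault lies in how the objectives are worded.

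Much of this stands. A reader might infer that the trial has no sound treatment comparison, or that no significant result could support any conclusion. The documents do not support that: a significant interaction would support a difference between the two programmes. Nor does the article state that patients will be declared normalised or that effectiveness has been shown; it poses a question and a hypothesis. What the reply does not meet is that the Discussion puts the between-programme comparison second, after a main question that the interaction cannot answer.

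On mechanisms, regression to the mean bears mainly on pain and disability, since entry is selected on pain (3 to 6 on the visual analogue scale) and not on kinematics. Retest learning may be small for a movement that the Introduction says workers may make about 60 times a day, and one investigator places all markers. These points argue for a smaller drift in the kinematic outcomes, but they do not supply a control for it.

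Initial Assessment is also open about the asymptomatic group being a baseline reference. That disclosure is fair, but it sits badly with using the group in a post-treatment test. Whether to test against that reference at all is a matter of preference.

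**Conclusion.** The concern holds as a mismatch between the stated main question and the randomised design. The interaction is valid but answers core versus general only. The time effect and the three-group ANOVA are the only planned routes to effectiveness itself, and neither separates exercise from other causes of change. With no exercise effect and an assumed drift of 0.2 to 0.3 SD, the core-arm pre-post test is significant in roughly 11% to 40% of trials and the pooled time effect in roughly 18% to 71%, for r between 0.5 and 0.8. These sizes rest on assumed drift and correlation, and would fall to 5% with no drift. The inability of the time effect to tell drift from treatment does not depend on those assumptions.

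**What to change.** 1. State the primary question as core minus general, estimated as the post-treatment difference adjusted for baseline (ANCOVA). This replaces or sits beside the planned interaction, whose variance is 1.33 times as large at r = 0.5 and 1.18 times at r = 0.7.
2. Report change within each arm as uncontrolled, and not as evidence that a programme is effective. Reword the main question and the hypothesis in the Introduction and Discussion to match.
3. Do not use the three-group ANOVA for core versus general.
4. Report post-treatment patients against asymptomatic participants as mean differences with 95% CIs, name the latter as a reference group measured once at baseline, and do not read non-significance as recovery.

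The cost is wording and analysis only, with no added participants or visits. The permissible conclusion becomes narrower: how core stabilisation compares with general exercise, and not whether either works. It also puts the weight on a demanding contrast. With 15 per arm, a two-sided t test on change has 80% power only for a difference of 1.06 SD of change.
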